# Australian Implementation of the Teaching Personal and Social Responsibility Pedagogical Model in Physical Education: Protocol for a Nonrandomized Controlled Trial

**DOI:** 10.2196/67924

**Published:** 2025-09-03

**Keywords:** teaching personal and social responsibility, social, physical education, intervention, high school

## Abstract

**Background:**

Interventions targeting the psychomotor domain of learning have been the most dominant in the physical education (PE) discipline. However, as PE also incorporates a holistic perspective of student development, a gap has emerged where interventions targeting social outcomes are not frequently analysed. Social outcomes have been of particular interest for interventions conducted in PE.

**Objective:**

This study will evaluate the impact of an intervention designed to enhance social outcomes among Australian school students. The intervention will be shaped by the teaching personal and social responsibility (TPSR) framework. This framework has lacked representation within the Australian context, creating a gap and an opportunity to explore its impact on the social behaviors of Australian students.

**Methods:**

This study will use a nonrandomized controlled trial design with a qualitative evaluation to assess feasibility and acceptability. Data will be collected through student surveys, student focus groups, and teacher reflection journals. Two schools in New South Wales, Australia, will participate by implementing the TPSR framework in their programs. Schools will include classes in stages 3 and 4 of the intervention, involving approximately 90 students from each school. Both schools are located in Sydney, New South Wales: one is a government high school, and the other is an independent K-12 school. To address feasibility and accessibility concerns, the intervention will be delivered during regularly scheduled PE classes. It will be facilitated by students’ regular PE teachers, who will also participate in ongoing professional development and be involved in a co-design process with the research team. Primary outcomes include reporting on personal responsibility, social responsibility, and leadership behaviors, measured using two tools: (1) the Tool for Assessing Responsibility-Based Education and (2) the Personal and Social Responsibility Questionnaire. A secondary outcome, enjoyment, will be assessed using the Physical Activity Enjoyment Scale–Physical Education version. Feasibility and accessibility will also be examined as secondary outcomes.

**Results:**

This intervention study will demonstrate the impact of TPSR on social outcomes among Australian school participants. Students will also receive a briefing, and parental permission will be sought before intervention commencement. Students will be involved in the intervention for the duration of term 3 (10 weeks).

**Conclusions:**

This protocol paper outlines the approach to implementing and evaluating the TPSR intervention among Australian school participants. One anticipated strength of the intervention is the ability to apply the framework to different settings, including schools, school sport, and community organizations. Longitudinal follow-up assessment will be critical in determining the long-term impact of the intervention on behavioral changes among participants.

**Trial Registration:**

Australian New Zealand Clinical Trials Registry ACTRN12624000858594p; anzctr.org.au/Trial/Registration/TrialReview.aspx?id=387883

**International Registered Report Identifier (IRRID):**

PRR1-10.2196/67924

## Introduction

### Background

The aim of physical education (PE) lessons is to establish lifelong habits and behaviors that lead to positive health outcomes [1]. Benefits of youth participation in PE lessons include improvements in cognitive development and learning [2]; social development [3]; and a range of physiological benefits such as improved coordination, balance, weight loss, and cardiorespiratory fitness [4]. Another benefit of participation in PE lessons is access to subject matter experts such as PE teachers who can correct movement, give feedback, and influence engagement and participation [5]. However, the literature suggests that young people become disengaged in PE as they get older, which may limit the achievement of a range of cognitive, affective, social, and psychomotor outcomes [6]. To remedy this decline, emerging literature suggests that a way to re-engage students in PE may be through an emphasis on interventions with outcomes that enhance student achievement across a range of learning domains [7].

PE interventions conducted in schools have been a leading method used by researchers to analyze emerging trends in the health of young people [4,7,8]. Interventions can be categorized as psychomotor, affective, social, and cognitive, with the psychomotor domain being the most dominant in PE-based research and interventions [7]. This is evidenced by a systematic review conducted by Dudley et al [7], who found that psychomotor interventions embedded in PE settings made up 38% of the included studies. The authors suggested that future research should target other aspects of learning, such as confidence and competence, to further support young people’s development and prepare them for adulthood [7]. This argument is also supported by the Australian Curriculum: Health and Physical Education (AC: HPE) as well as its statewide equivalent, the New South Wales (NSW) K-10 personal development, health, and physical education (PDHPE) syllabus, both of which have made amendments to include a stronger emphasis on social outcomes (eg, developing empathy, relationship skills, and connectedness) in conjunction with psychomotor outcomes, which have always been prioritized in PE lessons [9]. The recently revised NSW PDHPE syllabus also features a specific strand targeting social outcomes—respectful relationships—with the sole focus of addressing and strengthening social behaviors of students [9].

Interventions targeting social outcomes in PE are not as prevalent as those targeting psychomotor outcomes, but existing studies, which are scattered within the literature, have demonstrated positive findings [10-12]. In the systematic review by Dudley et al [7], which reported on PE interventions and a range of outcomes, only 25 of the 135 included studies assessed the impact of PE on social outcomes. The study by Dudley et al [7] is important because it not only highlights emerging studies on previously underrepresented interventions targeting social outcomes but also demonstrates the gap in the literature and an opportunity for further research.

Furthermore, interventions targeting social outcomes are reported to have strong associations between student motivation and the development of autonomy through PE lessons [13]. Research suggests that students who develop skills such as leadership and responsibility behaviors experience smoother transitions from school to adult life [14]. Other research has found that student self-esteem and physical self-concept were improved through involvement in interventions targeting social outcomes [15]. However, a criticism of social interventions has been the issue of transfer, that is, whether positive effects last beyond the intervention or are merely a result of a novelty effect, which has been noted in studies featuring PE pedagogical models such as the sport education model and teaching games for understanding. To counter this criticism, the teaching personal and social responsibility (TPSR) framework has been chosen, as it has a domain dedicated to promoting transfer [16]. This framework has been used in the PE context to improve the social skills of participants and may be able to address the gap in the literature by targeting social outcomes with lasting benefits [17,18]. The sport education model and the teaching games for understanding model have been used in interventions targeting social outcomes in a variety of contexts; however, “transfer” underpins all other levels of the TPSR framework and aims to address social outcomes as a life skill, rather than as a tool for PE class [19]. Furthermore, TPSR differs from other social frameworks, as its levels are more fluid and nonhierarchical, allowing students to move in and out of the TPSR domains, rather than following a step-by-step process of development [19].

TPSR is a pedagogical framework designed by Hellison to engage students with low socioeconomic status (SES) from urban communities in PE lessons [10,16]. One of the main goals of the TPSR framework is to encourage students to apply the skills learned throughout the intervention to other key learning areas, as well as life outside the school setting [16]. TPSR aims to promote student autonomy and teach students to take responsibility for their learning [17]. The framework aims to improve skills such as empathy and leadership as well as developing and maintaining relationships, which strongly mirrors the goals and rationale of the NSW PDHPE K-10 syllabus and the AC: HPE [9,16,20]. The framework has been constructed using five levels: (1) respect for the rights and feelings of others, (2) effort and teamwork, (3) self-direction and goal setting, (4) helping and leadership, and (5) transfer [16,17]. There are also four themes for each program—(1) a strong teacher-student relationship, (2) empowering students, (3) integrating responsibility into physical activity, and (4) promoting the transfer of responsibility—which align strongly with the AC: HPE and the NSW K-10 PDHPE syllabus [9,16,17,20]. Due to a strong link between the TPSR framework and the Australian curricula, future interventions should aim to plan, implement, and test the effect of TPSR in Australian schools. Australian schools are a desirable setting for interventions using TPSR, given the similarities to the environments identified by Hellison [21] in his work with disengaged students from low-SES backgrounds. Furthermore, schools in the western suburbs of Sydney serve a high proportion of students with low SES and have noted difficulty with engagement and integration from both student and teacher perspectives [22,23]. However, TPSR implementation in Australian schools has seldom been reported, and interventions using social frameworks in PE lessons are scarce.

International research using the TPSR framework has shown promising findings [12,18,24,25]. In a systematic review, a Turkish study found that TPSR-based interventions improved students’ efficacy as well as interpersonal interactions and emotional regulation when dealing with other students and adults and in contexts where they were required to recognize and express emotion [18]. Similarly, research from Taiwan found that adherence to the TPSR framework in PE settings improved the self-efficacy and efficacy-like behaviors of middle school students [24]. A study in the United States found that students’ socially responsible behaviors, such as emotional regulation, problem-solving, and the promotion of social norms, improved as a result of TPSR-based interventions [25]. TPRS has further demonstrated an increase in motivation for engaging in PE classes, with research in Spain demonstrating that students had more positive perceptions of their athleticism as well as showed improvements in leadership and decision-making skills as a result of participation in the intervention [12]. International literature demonstrates a clear improvement in many social outcomes due to participation in interventions that apply the TPRS framework. In addition, a notable point of difference between TPSR and other social frameworks is the transfer domain, which could be particularly important when implementing a TPSR intervention in the Australian context.

### Objectives

The aim of the study is to conduct a research intervention that will reveal the impact of the TPSR framework on students’ social outcomes in the Australian context. This research is significant because it will be the first time that TPSR has been tested in NSW high schools. The study will use a nonrandomized controlled trial design to determine feasibility and acceptability aspects.

## Methods

### Trial Registration

The study has been registered with the Australian New Zealand Clinical Trials Registry (ACTRN12624000858594p) and was approved on June 11, 2024.

### Ethical Considerations

This study has been approved by the University of Sydney Human Research Ethics Committee (2024/HE000496).

Students and parents will sign consent forms before taking part in this study. Students who do not want to participate will still attend PE lessons, but no data will be collected from them. Participants may withdraw from the intervention at any time by informing their facilitating teacher.

All participants will be deidentified, and no information about individual students or their school will be disclosed. Data will be password protected and securely stored by the principal investigator.

No compensation will be offered to participants or participating schools.

### Study Design

The protocol was developed according to the SPIRIT (Standard Protocol Items: Recommended for Interventional Trials) statement (Multimedia Appendix 1).

The study will use a nonrandomized controlled trial design with a qualitative evaluation to assess feasibility and acceptability. This method has been chosen for several reasons. First, one of the criticisms against the TPSR model is that it favors qualitative studies and has been underresearched using quantitative methodologies [11]. To address this, we will use both qualitative and quantitative methods in this study. The concern regarding the limited use of quantitative approaches was echoed in a systematic review on TPSR interventions that found that only 4 of the 22 included studies used exclusively quantitative methods, questioning the validity of the framework outside of qualitative research [26]. Studies have consistently called for greater use of quantitative analysis of the TPSR framework in research [10,11,26]. Furthermore, to obtain the most accurate representation of the effect of the framework in Australian schools, teachers, and students, this approach is deemed most suitable because it uses both qualitative and quantitative analysis and is able to factor in a complex landscape such as education [27]. In this study, data will be collected through student surveys, focus groups, teacher reflection journals, and the Tool for Assessing Responsibility-Based Education (TARE).

We will recruit at least 6 classes from each school participating in the intervention, which will amount to approximately 3 classes in the control group and 3 in the experimental group (Figure 1).

Upon recruitment of the schools and selection of individual classes by each principal, researchers will collaborate with intervention facilitators to implement the TPSR framework during the intervention “season.” Table 1 presents example strategies that can be implemented in a TPSR study and will be shared with teachers during the co-design process.

A timeline of the intervention is presented in Table 2.

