### Outcomes

The primary outcomes addressed within the intervention are personal responsibility, social responsibility, and leadership, reflecting the levels of the TPSR framework. The secondary outcomes include enjoyment, feasibility, and acceptability. To obtain a comprehensive analysis of the TPSR framework within a school system, the proposed outcomes will provide valuable insights into how the framework influences student behavior and overall intervention effectiveness.

Baseline characteristics will include age, gender, boarding status (boarding vs nonboarding), school type, and SES (via postcode).

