### Participants

The participants in this study will be students from years 5, 6, and 8. Each intervention group in the study will need to have 77 students and a matched control group of the same size to detect 2-tailed statistical significance (*P*<.05) with 80% power (1−β=0.8). Two schools in the western suburbs of Sydney have been recruited to participate in the study: one is a government high school, and the other is an independent K-12 school. They have been chosen through professional networks who expressed interest in the TPSR study. Students in NSW generally participate in 1 PE lesson per week, which is where the intervention will take place. PE lessons in NSW high schools are delivered to students from years 7 to 10 and focus on skills development, alongside one or two sport lessons focused on game play.

Consent will be obtained from parents, students, and the school principals in line with the ethics requirements of the University of Sydney. Participants’ personal information and school names will be deidentified in all publications arising from the study. Students and teachers will also be briefed on the intervention before study commencement and given the opportunity to ask questions. Participants will be allowed to withdraw from the intervention at any time. All data collected, including data from focus interviews, surveys, meeting minutes, and consent forms, will be stored securely and encrypted with a password. If parents request details of intervention results, a lay summary will be provided.

Fidelity and acceptability will be addressed through teacher expertise and training, intervention location, timetabling, and time spent on the intervention. Teachers will participate in a professional development program before starting the intervention. The purpose of this program is to familiarize teachers with the TPSR framework and to facilitate the co-design of strategies and activities to integrate the framework into programs. This approach also means that students do not have to build relationships with or adapt to outside facilitators. Furthermore, it does not incur additional funding for the school or research team. The professional development program will comprise a 3-hour, face-to-face learning block before the intervention and ongoing check-ins with teachers using Zoom (Zoom Video Communications, Inc) for the duration of the intervention.

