#### Quantitative Analysis

Quantitative data from the PSRQ, PACES-PE, and TPSR will be analyzed using SPSS software (version 30.0; IBM Corp). Internal consistency of the scales will be assessed using Cronbach α. The PSRQ will assess students’ self-perceived levels of personal and social responsibility, and the PACES-PE will assess enjoyment in PE. ANOVA will be conducted to compare mean scores before and after the intervention for both questionnaires. TARE data will be collected through lesson observations by the research team 3 times during the 10-week intervention period, and interrater reliability will be assessed using Cohen κ. Frequencies and mean scores of the TPSR strategies will be examined descriptively and across time to explore implementation fidelity. A repeated measures multivariate ANOVA will be performed to provide a more complex analysis of the findings and a more comprehensive view of how the intervention affects multiple variables simultaneously.

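### In a nonrandomised trial with classes chosen by principals, the stated ANOVA and MANOVA name no TPSR-versus-control contrast and use none of the listed baseline characteristics

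*Protocol article*

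**What the plan says.** **Design.** The Study Design section states: "The study will use a nonrandomized controlled trial design with a qualitative evaluation to assess feasibility and acceptability". Classes enter by "selection of individual classes by each principal". At least six classes are planned per school, giving "approximately 3 classes in the control group and 3 in the experimental group". No rule for placing a class in one arm or the other is given.

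**Schools and students.** Of the two schools, the Participants section says: "They have been chosen through professional networks who expressed interest in the TPSR study". One is a government high school and the other an independent K-12 school. Students are in Years 5, 6 and 8. Each intervention group "will need to have 77 students and a matched control group of the same size", for a two-sided 5% test with 80% power. No matching variable or procedure is described.

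**Baseline data.** The Outcomes section says: "Baseline characteristics will include age, gender, boarding status (boarding vs nonboarding), school type, and SES (via postcode".

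**Analysis.** The Quantitative Analysis section says: "ANOVA will be conducted to compare mean scores before and after the intervention for both questionnaires". It adds a repeated measures multivariate ANOVA to look at several variables together. Neither sentence names study arm, a group-by-time term, the pretest as a covariate, or any baseline characteristic. The Strengths and Limitations section does not mention selection or confounding.

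**The concern.** Without randomisation, the two arms can differ at entry for reasons unrelated to TPSR. A principal might choose cooperative classes, or disengaged ones, and year levels might fall unevenly across arms. Years 5 and 6 can come only from the K-12 school, because the other school is a high school. With about three classes per arm in each school, an even spread of year level cannot be relied on.

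The design offers three possible protections: controls within the same school, use of the pretest, and adjustment for measured characteristics. The first is present. The second is only implied, because the text never says that change is compared between arms; read literally, the ANOVA sentence compares times rather than arms. The third is absent from the stated analyses, although the variables are to be collected. The word matched suggests a fourth protection, but no factor is given for it. What is at stake is whether a reported TPSR effect partly reflects who was in the classes.

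**Working it through.** **Inputs from the article.** 77 per group, two-sided 5%, 80% power; about three classes per arm per school; two schools; Years 5, 6 and 8. No effect size, SD, baseline imbalance or pre/post correlation is given.

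**Assumptions.** Entry difference in the outcome (TPSR minus control) D = 0.2 to 0.3 SD; pre/post correlation ρ = 0.6, with 0.5 and 0.7 as a range; no true effect. SDs are taken as equal at both times. Rejection rates treat students as independent.

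**Step 1: the plan's own figure.** Without an effect size, 77 cannot be reproduced forwards. Solving backwards, (1.960 + 0.842) × √(2/77) = 0.4515 SD; the t-test version gives 0.454 SD. The latter serves as the yardstick.

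**Step 2: change compared between arms (group-by-time).**
- If the entry difference is stable, the bias is D − D = 0.
- If both arms regress to a common mean, the bias is ρD − D = −(1 − ρ)D.

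| ρ | D = 0.2 | D = 0.3 | Share of 0.454 |
|---|---|---|---|
| 0.5 | −0.10 | −0.15 | 22 to 33% |
| 0.6 | −0.08 | −0.12 | 18 to 26% |
| 0.7 | −0.06 | −0.09 | 13 to 20% |

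The sign is opposite to the entry difference: an arm that starts higher looks less improved. With standard error √(2(1 − ρ) × 2/77), the nominal 5% test rejects 9.5% (D = 0.2) to 15% (D = 0.3) of the time at ρ = 0.5, and 7.7% to 11% at ρ = 0.7.

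**Step 3: differential change by a characteristic.** Bias = (difference between arms in the share with the characteristic) × (difference in change linked to it). Assuming 20 to 50 percentage points and 0.2 to 0.3 SD, this runs from 0.2 × 0.2 = 0.04 SD to 0.5 × 0.3 = 0.15 SD. Comparing change does not remove this.

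**Step 4: posttest-only comparison, for contrast.** The bias would be ρD = 0.6 × 0.2 = 0.12 to 0.6 × 0.3 = 0.18 SD (26 to 40% of 0.454) under regression to a common mean, or the full 0.2 to 0.3 SD if the difference is stable. The article does not name this comparison.

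**Step 5: what pretest adjustment does.** The adjusted estimate is the posttest difference minus ρ times the pretest difference. Under regression to a common mean the bias is ρD − ρD = 0. Under a stable difference it is D − ρD = 0.4D, or +0.08 to +0.12 SD at ρ = 0.6. The adjusted and change estimates therefore rest on different assumptions, which is a reason to report both.

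**The case against.** The strongest reply is that the named analyses use the pretest, so a stable entry difference cancels once group-by-time is read as the effect. That is correct. A reader might infer that entry differences pass straight into the estimate, at 26 to 40% of the detectable effect or more. The documents do not support this, because it needs a posttest-only comparison that the Quantitative Analysis section does not name.

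Four other strong readings also go too far.
- *Nothing balances the arms.* The class split is described for each school, so both arms come from both schools and school type is roughly balanced.
- *Principals assign classes to arms, or a Year 5 versus Year 6 comparison is planned.* The text says only that principals select classes. How classes reach an arm is unstated, and a year-level imbalance is left open rather than planned.
- *The control group is matched on size alone.* The article gives no other factor, but it does not rule one out.
- *The baseline characteristics are excluded from the analysis.* The article is silent on this.

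It can also be said that a covariate list is the kind of detail an article leaves to the analysis plan. For a randomised trial that would settle the matter. Here control of confounding is central to the design, the analyses that the article does fix are unadjusted, and the between-arm contrast is not named at all. The point therefore stands in its narrower form.

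**Conclusion.** The point holds as a limited one. As written, the plan secures neither the partial protection of a group-by-time contrast nor adjustment for characteristics it intends to collect. For a change comparison the bias from regression to the mean ranges from zero (stable entry difference) to about -0.08 to -0.12 SD, or 18 to 26% of the roughly 0.45 SD implied by 77 per group. Differential change by year level, gender, boarding status or SES could add bias in either direction, illustrated at 0.04 to 0.15 SD. All of these sizes rest on assumed imbalances and correlations. The absence of a named contrast and of covariates, and the undefined word matched, rest on the text alone.

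**What to change.** In the Quantitative Analysis section, make the primary estimate the TPSR-versus-control contrast adjusted for pretest score, school, year level (or age), gender, boarding status and postcode SES. Report the unadjusted group-by-time estimate as a sensitivity analysis, and say that the two rest on different assumptions about entry differences. Fix this before the outcome data are analysed. In the Participants section, delete the word matched from "a matched control group of the same size" or state the matching factor.

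The data cost is close to nil. The characteristics are listed under Outcomes, year level is known from eligibility, and a completed pretest is an eligibility condition.

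The statistical cost is some loss of degrees of freedom. Year level also partly overlaps with school, because Years 5 and 6 exist only in the K-12 school. With about 12 classes in all, adjustment cannot separate the effects if a year level falls wholly in one arm, and the report should then say so. Rearranging classes into year-matched pairs is no longer a practical remedy: the Results section says recruitment ended in December 2024 and data collection began in August 2025.
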